### Women's views and information needs

To obtain data on Australian women's views and information needs about ECV we undertook a cross-sectional study of women's knowledge, attitudes and decision-making preferences for the management of breech presentation[28]. Of 174 pregnant women respondents (97% response rate), almost 90% preferred vaginal delivery but only 66% had heard of ECV. After a brief written explanation of ECV 39% would choose ECV, 22% were unsure and 39% would not choose ECV. The reasons for not choosing ECV included concerns about safety for the baby (13%), that ECV doesn't guarantee vaginal delivery (12%) and preference for a caesarean section anyway (8%). Importantly, 95% of pregnant women wanted involvement in decision-making about breech presentation.

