### Decision making and breech presentation

The management of breech presentation is a clinical decision that fulfils Eddy's criteria for a decision in which patients' values and preferences should be included[40]. The outcomes for the breech management options (ECV and planned CS), and women's preferences for the relative value of benefits compared to risks are variable and could result in decisional conflict. For such a clinical decision, a decision aid would be expected to improve patient knowledge and create more realistic expectations, to reduce decisional conflict and to stimulate patients to be more active in decision making without increasing anxiety[35].

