### Development and pilot-testing of the decision aid

In 2002 we developed an evidence-based decision aid for women with a breech presentation in late pregnancy. In developing the decision aid we utilised the NHMRC guideline "How to prepare and present information for consumers of health services"[41] (developed in 1999 by a team led by [name]), and the Ottawa framework established and rigorously tested by the Ottawa Health Decision Center[34]. The decision aid includes a Workbook, Audiotape/CD and Worksheet. The workbook highlights key points (similar to a slide presentation) and the audiotape/CD connects these points in a narrative format, providing more detail than the workbook. The worksheet is a one-page sheet to be completed by the woman to record her decision making steps, to list any questions she needs answered before deciding, and to indicate her preferred role in this decision (she should decide, her health care provider should decide, they should decide together). Most importantly, the DA was designed to be non-directive in that it did not aim to steer the user towards any one option or increase or decrease intervention rates but rather act as an adjunct to care

The decision aid was designed for women to use at home or in the clinical setting, and takes about 30 minutes to complete. The aural component is available on both audiotapes and CDs so participants can choose which they prefer to use. After working through the decision aid, the woman brings her completed worksheet to her next antenatal appointment to discuss her provisional decision with her health care provider before arriving at her final decision. The worksheet is also useful for the practitioner, who can see rapidly from it what evidence the patient has considered, what her values and preferences on this topic are and which way she is leaning in her decision.

The decision aid was developed, pilot tested and revised with extensive consumer involvement, as outlined in the NHMRC guideline on preparing information for consumers[41]. Content was largely driven by consumers' questions and information needs as determined from the cross-sectional study[28] and from the process of drafting, pilot testing and re-drafting.

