## Methods

### Specific aim

To compare the relative effectiveness of the decision aid with standard care in relation to women's knowledge, expectations, satisfaction with and participation in decision making, anxiety and decisional conflict. Secondary outcomes will include service utilisation and perinatal outcomes.

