#### Primary outcomes

The effectiveness of risk communication to aid patient decision making is best assessed by a combination of cognitive, affective and behavioural outcomes[43]. Thus the primary outcomes of the this study will be

• cognitive: change in knowledge and realistic expectations of the management options and possible benefits and risks of each option

• affective: anxiety, satisfaction with the decision, participation in decision-making and the amount of decisional conflict (uncertainty about which course of action to choose) experienced

• behavioural: actual decision taken and acted upon (see secondary outcomes)

Measures of knowledge and realistic expectations about options for the management of breech presentation and the benefits and risks of ECV will be specific to this project. Thus we will need to develop, and test these measures as part of the project.

Anxiety will be measured by the state component of the short Spielberger anxiety scale which has been extensively used and validated[42]. We do not anticipate the decision aid will increase women's anxiety but it is nevertheless important to document any increase or decrease in anxiety attributable to the decision aid.

Satisfaction with the decision will be assessed using the Satisfaction with Decision Scale. Satisfaction with Decision Scale (a very brief six item scale with high reliability) was developed specifically to assess satisfaction with health care decisions[44].

Participation in decision-making will be ascertained using the five-item Degner Control Preferences Scale[45]. This allows respondents to specify the degree of control in decision-making they wish to assume with their doctor.

Decisional conflict will be assessed by the Decisional Conflict Scale which has established reliability, good psychometric properties and is short (16 items)[46]. It has been used to evaluate a range of decision aids[35].

Because the decision about ECV must be made within a short timeframe, the outcomes will be measured as soon as practical after the consultation in which the ECV decision was made – prior to the next antenatal visit. For the primary outcomes this will be within one week of the decision being made (Figure 1, 1^st ^follow-up).

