#### Data analysis

Analyses will be by intention to treat, including withdrawals and losses to follow-up. Study groups will be compared in terms of baseline characteristics. As this is a randomised trial, we would anticipate minimal differences in baseline characteristics. If however, important differences are found, these potential confounders will be adjusted for in the analysis of outcomes. For the primary outcomes, the mean score for each measure for each group will be compared using t-tests. If adjustment for confounders is needed a multiple linear regression model will be used. The secondary outcomes will be compared using chi-square tests of significance for categorical data and t-tests for continuous data. If adjustment for confounding is necessary logistic regression and multiple linear regression will be used respectively.

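### Participation in decision-making is an outcome of the trial, but the only instrument named for it records the role women would like, not the role they had

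*Protocol article*

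**What the plan says.** The Specific aim section says the arms will be compared on "women's knowledge, expectations, satisfaction with and participation in decision making, anxiety and decisional conflict". Under Primary outcomes the affective group reads "affective: anxiety, satisfaction with the decision, participation in decision-making and the amount of decisional conflict", so participation is listed there as primary.

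The same section names the instrument: "Participation in decision-making will be ascertained using the five-item Degner Control Preferences Scale". The next sentence says what it captures: "This allows respondents to specify the degree of control in decision-making they wish to assume with their doctor".

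The section on decision making and breech presentation gives the effect expected of an aid, which includes "to stimulate patients to be more active in decision making without increasing anxiety".

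For analysis, the Data analysis section has one general rule: "For the primary outcomes, the mean score for each measure for each group will be compared using t-tests".

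**The concern.** The aim and the expected effect concern what women do when the decision is made. The instrument, in the article's own description, concerns what they would like to do. The two can move apart. A woman may want to share the decision and find it made for her, or may take a larger part than she wished.

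The risk lies in interpretation. If the arms do not differ on the scale, the report could say that the aid had no effect on participation, although participation was not measured. If they differ, the report could say that the aid made women more active, when only their stated wishes differed.

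**Working it through.** No arithmetic decides this point. The check is whether any measure in the article records the role actually taken, in both arms.

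1. **Baseline data collection.** Age, parity, socio-demographic data, education, knowledge and anxiety. Neither preferred nor actual role is listed, so a later role cannot be set against an earlier preference.
2. **Primary outcomes, first follow-up.** Knowledge and expectations, anxiety, satisfaction, decisional conflict and the Control Preferences Scale. Only the last concerns role, and it is described as a wish. The behavioural outcome is which decision was taken and acted on, not who took it.
3. **Second follow-up, 12–16 weeks postpartum.** Satisfaction and anxiety are measured again. This questionnaire also covers women's views of how the decision was reached, but the stated measure is satisfaction, not role.
4. **Secondary outcomes.** Service use and pregnancy outcomes only.
5. **Decision aid worksheet.** It asks the woman "to indicate her preferred role in this decision (she should decide, her health care provider should decide, they should decide together". This too is a preference, and only women given the aid complete it.

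The search finds no measure of actual role.

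**Status of the outcome.** Specific aim and Primary outcomes include participation. The abstract names knowledge, decisional conflict, anxiety and satisfaction as primary, and the four primary hypotheses cover the same four. The sample size rests on decisional conflict and knowledge. For decisional conflict, with two-sided 0.05 and power 0.8, n = 2 × (1.960 + 0.842)² × 13.25² / 5.75² ≈ 83.4, which rounds up to the stated 84 per arm. No target difference is given for participation, so the sample size does not depend on it.

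**When actual role could be asked.** The sections disagree on whether the first questionnaire precedes or follows the decision:

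- Primary outcomes places it after the consultation at which the ECV decision was made, within one week of that decision.
- The section on developing the aid has the woman take a provisional decision to her next antenatal visit and settle it there with her provider.
- Follow-up 1 and the blinding section have the first questionnaire completed before that next consultation. Follow-up 1 also places the obstetrician's discussion with women choosing ECV after the questionnaire.

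On the first account, a past-tense question about role can be answered at the first follow-up. On the others, some women would be asked about a decision not yet final.

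**The case against.** The strongest reply is that this is a condensed article. The questionnaire is not shown, and the sentence describes the scale in general, so the trial's items might ask about the role taken. That is possible, but nothing shown says so. The article assigns the scale to this outcome and says what it records. If the items were reworded, the description would still need correcting.

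A second reply is that no stated hypothesis rests on participation, so little depends on it. This stands in part: it limits the consequences and makes an unqualified claim of primary status too strong. But the outcome is in the aim and in the primary list, and the mismatch would remain if it were secondary.

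A third is that an actual-role question may come too early at the first follow-up. This stands, and the remedy has to allow for it.

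A reader might also fault the planned t-test because the scale may be read as ordered levels of control. Comparing mean scores on such a scale with about 84 women per arm is common and usually adequate. An ordinal model is an option, not the correction of an error.

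**Conclusion.** The point holds as a mismatch between outcome and instrument. Followed as written, the plan cannot show whether the aid changed women's participation; it can show only whether it changed the control they say they want. This rests on the article's own description of the scale and on the absence of any other role measure for both arms. It should be corrected, but it does not affect the comparisons of knowledge, decisional conflict, anxiety or satisfaction.

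A reader might infer more from the background survey, where "95% of pregnant women wanted involvement in decision-making about breech presentation": that the scale is already near its ceiling, with at most 5 points left to gain and low power. The documents do not support this. The survey figure summarises any wish for involvement among an earlier sample of pregnant women. It is not a distribution on the five-item scale and not a figure for trial controls. Wanting involvement could cover both sharing the decision and making it alone, so there may be room to move within the 95%. The plan does not dichotomise the scale, and any target proportion above 95% would have to be invented. No power figure is therefore attached to this point.

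**What to change.** - Reconcile the timing of the first questionnaire relative to the decision across the sections on developing the aid, Follow-up 1, blinding and Primary outcomes.
- In both arms, add one question on the role the woman actually had in the breech decision, offering the scale's five options in the past tense. Ask it at the first follow-up if that falls after the decision. Otherwise, or in addition, ask it in the 12–16 week postpartum questionnaire.
- Use actual role as the participation outcome, or its agreement with preferred role. The second choice needs a preferred-role question at baseline, before the aid can alter the preference. An ordinal analysis is optional.
- If no such question is added, rename the outcome preferred role and draw no conclusion about participation.
- State in the abstract, aim, hypotheses and outcome list alike whether the outcome is primary.

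The cost is one or two extra questions in existing questionnaires, with no extra visits or staff. If actual role is asked only postpartum, the answer depends on recall and may be coloured by how the birth went.

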#### Secondary outcomes

The aim of the decision aid is to assist patient decision making, and not to influence the direction of the decision taken. Nevertheless, we think it is important to collect service utilisation and pregnancy outcome data so we will record and compare the numbers of ECVs undergone and ECV success rate in both arms of the study, as well as recording and comparing rates of pregnancy complications and perinatal outcomes. Data on ECVs are already prospectively collected for quality assurance, these include fetal lie, parity, success rates and complications. Other perinatal outcomes will be obtained (with informed consent) from the existing computerised obstetric database. These outcomes include mode of delivery (vaginal, emergency or planned CS), enrolment to delivery interval, gestational age, birthweight, Apgar scores, perinatal deaths, Neonatal Intensive Care Unit admission, maternal haemorrhage (antepartum or postpartum) and length of stay.

### Statistical issues

#### Sample size

Sample size calculations for the trial (significance 0.05, power 0.8) were determined using the mean difference we would like to detect in women's decisional conflict scores and knowledge of options and outcomes. Compared with usual care, decisional conflict was shown in the most current systematic review to be significantly reduced by decision aids; the meta-analysed mean difference was -5.75, 95%CI -8.63, -2.87 (on a scale ranging from 1 lowest to 5 highest decisional conflict; median standard deviation 13.25)[48]. Assuming a mean difference of -5.75 and standard deviation 13.25, we would need approximately 84 women in each arm to demonstrate changes in decisional conflict. The meta-analysis also showed that for nine trials comparing decision aids and usual care, decision aids improved average knowledge scores by 18.75 points (out of 100) (95%CI 13.1 to 24.4, median standard deviation 20)[48]. To show such a difference, assuming mean difference of 18.75 and standard deviation of 20, would require only 18 women in each arm. Because we would like to be able to show differences in decisional conflict if they exist, we have used the larger sample size estimate. Although follow-up will be relatively short term, there will inevitably be some loss to follow-up. To allow for 10% loss to follow-up the sample size calculated above (84) is inflated by 10% to give the effective sample size of 92 women per arm and a total sample of 184 for the trial. This sample size is different from our original application for funding. Originally, we estimated a sample size of 310 women (155 in each arm). This was based on results from a 1999 systematic review of only 2 trials of decision aids versus usual care that had assessed decisional conflict[35]. Subsequent to the submission (January 2001) and funding of this protocol (March 2002) the systematic review was updated (2002) incorporating 6 trials that assessed decisional conflict[48]. At that time we revised the sample size estimate to incorporate the most current research evidence available. Ethics approval was obtained for the protocol amendment.

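### The decisional conflict planning values (difference -5.75, SD 13.25) cannot lie on the 1-to-5 scale the protocol gives for them; 84 per arm still follows if both share one metric

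*Protocol article*

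**What the plan says.** All the figures are in the protocol article under Statistical issues, Sample size.

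- The design values are "significance 0.05, power 0.8". Sidedness is not stated.
- For decisional conflict, the cited systematic review is reported as follows: "the meta-analysed mean difference was -5.75, 95%CI -8.63, -2.87". The metric and spread are then given as "on a scale ranging from 1 lowest to 5 highest decisional conflict; median standard deviation 13.25".
- The same two values become the planning assumption: "Assuming a mean difference of -5.75 and standard deviation 13.25, we would need approximately 84 women in each arm".
- Knowledge, reported out of 100 (difference 18.75, SD 20), needs 18 per arm. The larger decisional conflict figure therefore sets the trial size.
- Attrition of one woman in ten is then provided for in these words: "the sample size calculated above (84) is inflated by 10% to give the effective sample size of 92 women per arm". Both arms together make 184.
- The paragraph adds that the size was revised from 310 when the review was updated.

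Under Primary outcomes, the instrument is named as the 16-item Decisional Conflict Scale, with no scoring range. Under Data analysis, mean scores are to be compared by t-tests.

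**The concern.** The target difference is larger than the whole width of the scale it is said to be on, and the standard deviation is more than six times the largest value that scale allows. So the only statement the article makes about the metric of its sizing target is impossible.

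Two things are at stake. First, the sample-size calculation is free of units only when the difference and the standard deviation are on the same metric. The difference is a pooled estimate and the standard deviation is a median across trials. With the metric misstated, a reader cannot check that the two belong together. The same values also carried the revision from 310 to 184 women, a cut of 126/310 = 41%. Second, a reader of the results needs the target difference in the units in which this trial scores the scale, and the article does not give it.

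Separately, the loss allowance multiplies by 1.10 where it should divide by 0.90, and then rounds down.

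**Working it through.** **Inputs** (Sample size section): difference 5.75; SD 13.25; significance 0.05; power 0.80; 10% loss; equal arms. Two-sided testing is assumed, because the one-sided calculation gives 66 per arm and does not match the article.

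**1. Reproduce the article's figures.**
n per arm = 2 × (1.960 + 0.842)² × (SD/difference)²
- Decisional conflict: d = 5.75/13.25 = 0.434, so n = 83.4, rounded up to **84**, as stated. The t-based version gives 84.3.
- Knowledge: 2 × 7.85 × (20/18.75)² = 17.9, rounded up to **18**, as stated.

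**2. Test the values against a 1-to-5 scale.**
- Largest possible difference between two means: 5 − 1 = **4**. The stated 5.75 exceeds it.
- Largest possible standard deviation (half the scores at each end): (5 − 1)/2 = **2**. The stated 13.25 is 13.25/2 = 6.6 times that.
- The outer limit of the quoted interval, 8.63, also exceeds 4.

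The two values therefore cannot be on the stated scale.

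**3. Does this change n?**
Only SD/difference enters the formula. If both values are divided by the same constant, d stays at 0.434 and n stays at 84. If they came from metrics differing by a factor k, n would change by k² (up or down). The document neither shows nor excludes such a mismatch.

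**4. Loss allowance.**
- Article's method: 84 × 1.10 = 92.4, rounded down to 92.
- Evaluable at 10% loss: 92 × 0.90 = **82.8** per arm (165.6 in total, against 168).
- Loss that 92 per arm covers: 1 − 84/92 = **8.7%**.
- Number that retains 84: 84/0.90 = 93.3, so **94** per arm and 188 in total (94 × 0.90 = 84.6).

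Power for d = 0.434, two-sided 0.05:

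| Evaluable per arm | Normal approximation | t-test |
|---|---|---|
| 84 | 80.3% | 79.8% |
| 82.8 | 79.7% | 79.3% |

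The shortfall costs 0.5 to 0.6 percentage points.

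**The case against.** The strongest reply is that no design quantity depends on the faulty label. The 84 reproduces. The planned t-tests do not change under linear rescaling, and neither does the interim harm rule, which is a significance threshold (p < 0.01, one-tailed). The parenthesis describes the metric of the review's pooled difference, not how this trial will score its questionnaire; that scoring may properly be set out in the full protocol or analysis plan. On the loss allowance, the article says approximately 84 and describes its method openly. The 82.8 left after 10% loss falls only about half a woman per arm short of the unrounded 83.4.

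Most of this stands, and it limits the point. What it does not answer is that the stated metric is impossible, that nothing elsewhere in the article resolves it, and that the unit-free defence of 84 needs a common metric which the reader cannot verify.

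A reader might be tempted by three stronger inferences that the document does not support:

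- **That the trial is chasing a difference it could never observe.** The article does not say the trial will score 1 to 5. If it scores on whatever metric -5.75 came from, the target is attainable.
- **That the monitoring committee would judge results against 5.75.** Under Interim analysis, neither the harm rule nor the clause on stopping when no clear outcome will be obtained refers to a target difference.
- **That the target is too large by a known factor.** On an assumed 0–100 rescaling the 1-to-5 equivalents would be 5.75/25 = 0.23 and 13.25/25 = 0.53. On an assumed 16-to-80 item sum they would be 5.75/16 = 0.36 and 13.25/16 = 0.83. The resulting factors of 25 and 16 are only as good as those assumptions, because the article gives neither metric for this instrument.

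**Conclusion.** The contradiction is certain: a difference of 5.75 and a standard deviation of 13.25 exceed the limits of 4 and 2 on a 1-to-5 score, so the metric stated for the sizing target is wrong. The sample size is not shown to be wrong. The 84 per arm follows from d = 0.434 under two-sided testing, on the assumption that both values share one metric. Which metric the review used cannot be settled from the article.

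The loss-allowance slip is real but minor: 1.2 evaluable women per arm, and about 79.3–79.7% power where 84 would give 79.8–80.3%. It does not make this an underpowered trial.

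Severity: should-fix. The error affects the outcome that sizes the trial and is cheap to correct, but no stated test or stopping rule changes because of it.

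**What to change.** 1. Check the cited review and state the actual metric of -5.75 and of 13.25.
2. Confirm that both are on that metric. If they are not, recompute n from values that are.
3. State how this trial will score the Decisional Conflict Scale, and express the target difference and standard deviation in that scoring.
4. For loss to follow-up, keep 92 per arm and state power as about 79–80% at 10% loss, or note that 92 covers 8.7% loss and that 84/0.90 would give 94.

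The cost is one look at the cited review and one rewritten paragraph. If the two values share a metric and 92 per arm is kept, no more women are needed. Moving to 94 per arm would add four in total.
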